### Intervention

To facilitate deliberation about treatment options, the uterine fibroid Option Grid PDA is organized in a tabular format and is based on patients’ frequently asked questions, which were sourced by analyzing the research literature and by qualitative inquiry with stakeholders including gynecologists and 10 women experiencing symptoms of uterine fibroids.

The uterine fibroid tool is one of over 22 Option Grid decision aids developed and maintained by EBSCO Health. We helped EBSCO adapt the Option Grid for this study by following a multi-step Community Based Participatory Research (CBPR) approach. The tool (as of May 2019) compares seven treatment options (watch and wait, medicine with hormones, medicine without hormones, uterine artery embolization, endometrial ablation, myomectomy, and hysterectomy) and consists of answers to six frequently asked questions: (1) What does it involve? (2) Will I have less bleeding and pain? (3) Will the fibroids go away or get smaller (in size)? (4) Is it safe to get pregnant? (5) What are the side effects? and (6) What are the more serious risks? The uterine fibroid Option Grid is designed to be accessible to patients across socioeconomic and health literacy strata using plain language (readability of 6th grade or less). See Fig. 2 to view the text version of the Option Grid.

**Fig. 2 Fig2:**
[figure not shown]
The uterine fibroid Option Grid patient decision aid

There will be two versions of the uterine fibroid Option Grid available in this trial: (i) text and (ii) text with pictures (Picture Option Grid). The Picture Option Grid uses the same evidence as the text version while integrating images, thus utilizing pictorial superiority to help patients better understand and remember information [26]. Both the text and Picture Option Grid will be available to clinicians and patients on paper pads and integrated into the EHR, leading to a website where the clinician can select the uterine fibroid Option Grid and choose any number of treatment options specific to the patient to generate the comparison table. The online version also offers the clinician a standard phrase to document the presentation of the Option Grid to patients. It can be copied and pasted into the EHR, and the tool can also be sent via the patient portal or by email to the patient. The content and layout of the online Option Grid will be maintained to match that of the text and Picture Option Grid versions for the duration of the project period. The different versions provide clinicians with options, so they can choose the format that best suits their workflow. Both versions will be available in English and Spanish (see “Translation procedure” section for details).

Option Grid PDAs, in any of the different formats, are designed as catalysts for discussion between patients and clinicians to compare options and come to agreement about the best treatment choice.

### Translation procedure

The text and Picture Option Grid used in this study will be translated into Spanish using an adapted version of the Translate, Review, Adjudicate, Pretest, Document (TRAPD) translation procedure [27, 28]. Our translation approach will include four main stages: (i) Two suitably qualified native speakers of the target language create independent translations of the original text; (ii) a bilingual reviewer (who is a native speaker of the target language) compares the original text, translation 1, and translation 2 and either selects the preferred translation or produces a third translation that builds on the previous two; (iii) the bilingual reviewer meets with the project team to review and reconcile translations by consensus; (iv) the resulting translation is tested via cognitive debrief interviews with a small sample of patients fluent in the target language. Cognitive interview participants will each be offered a $10 honorarium.

### Outcomes and data collection

#### Primary outcome measure

The primary outcome measure is the number of eligible patients who receive the uterine fibroid Option Grid (three formats available).

Eligible patients will be identified in advance by the project team at each site through their outpatient scheduling systems. This process will enable us to determine the total number of patients who are eligible to participate in the study (the denominator). To calculate the number of patients who receive an Option Grid (numerator), we will provide each site with a box filled with text and Picture Option Grid paper pads. Pads will be available in every consultation room within each sites’ obstetrics-gynecology clinic. To use a paper-based Option Grid, the clinician will tear it from the pad and a numbered stub will remain where they will write their name and indicate if they are an attending clinician or a resident (see Fig. 3 for a mockup of the paper pad stub). The research assistant at each site will refer to the numbered stubs to document the number of patients who received an Option Grid on a weekly basis. The research assistant will keep a log of the numerator and denominator in an Excel file and will report the data back to the Dartmouth project staff on a weekly basis via the Qualtrics database.

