E. Complexity: as the number of steps, or the number of people or processes increases, so does the difficulty of implementation.	The Option Grid has been designed to be fast, frugal, and outwardly simple, so that it can fit into decision discussions that will benefit from accurate, accessible information.
F. Design quality and packaging: instills confidence in the intervention.	The EBSCO Option Grid has achieved high quality design with professional user centered graphic design.
G. Cost: investment, supply, and opportunity costs.	Investment will be related to the time taken to learn how to integrate the tool into the clinical workflow, a learning curve that has been observed to take a few interactions. The project will ensure adequate supply; future use will need to ensure online access for sustainability. We anticipate minimal disruption on opportunity costs—clinicians typically cover the type of information in Option Grids. The tool makes the exchange more efficient according to our evaluations. Evidence suggests that Option Grid decision aids do not typically increase consultation time as the content of the tool is information clinicians already provide to patients routinely.
II. Inner setting	
B. Networks and communication: The nature and quality of webs of social networks and the nature and quality of formal and informal communications within an organization.	Eligible patients will be identified using the site’s outpatient scheduling system in advance of their visit. Where possible, the eligible patients will be sent an Option Grid in advance of their appointment and will be instructed to bring the Option Grid to their appointment.
C. Culture: Norms, values, and basic assumptions of a given organization.	We want to help implement a process where patients are engaged in their treatment decisions “upfront” by receiving an intervention that can facilitate a discussion with their clinician regarding their treatment options.
D. Implementation climate: The absorptive capacity for change, shared receptivity of involved individuals to an intervention, and the extent to which use of that intervention will be rewarded, supported, and expected within their organization.	We will assess implementation climate by calculating the expected use of the intervention which is based on the volume of patients visiting each site who have been diagnosed with symptomatic uterine fibroids.

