### Participants

We will include physicians (attending or resident) who consent to participate in our implementation study and provide care to women with symptomatic uterine fibroids during the project duration at participating sites.

We will include patients showing new or recurrent symptoms of uterine fibroids (e.g., heavy menstrual bleeding, pelvic pressure or pain) who are seeking treatment and meet all of the following inclusion criteria: (i) assigned female sex at birth, (ii) at least 18 years of age, (iii) speak English or Spanish, and (iv) have the ability to complete short surveys online independent of assistance. We will not exclude pregnant patients. We will exclude postmenopausal patients because they may have different treatment options than those presented in the Option Grid PDA used in this study.

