**Fig. 3 Fig3:**

Paper-pad mockup to identify the number of eligible patients receiving the uterine fibroid Option Grid in the clinic

For sites with EHR access to the online uterine fibroid Option Grid, we will derive weblog data from EBSCO Health including the date and time the tool was generated; this data will be incorporated into measurement of the primary outcome.

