
**Table 2 Tab2:** Implementation sustainability outcome measures for patient outcomes

	Implementation phases		
	Pre	Active	Sustainability
Organizational readiness (Measuring Organizational Readiness for patient Engagement survey)	✓		
Clinician attitudes to PDAs (ADOPT: Attitudes toward Decision Aids fOr PatienTs survey)	✓	✓	✓
Percentage of eligible patients receiving intervention (primary outcome measure)	✓	✓	✓
Quality of shared decision-making process using Observer OPTION-5	✓	✓	
Utility of tools and approach (clinician interviews)		✓	✓
Normalization Process Theory: NOMAD Toolkit (interviews)	✓		✓
Intervention fidelity assessment using observer checklist		✓	
Patient outcomes			
Uterine Fibroid Symptom and Health-Related Quality of Life Questionnaire (UFS-QOL) symptom severity subscale (8-items)	✓	✓	
**collabo**RATE (three items)	✓	✓	
The Comprehensive Score for financial Toxicity (COST)—one selected item	✓	✓	
Resource utilization (ambulatory and hospital visits)	✓	✓	
Intended and received treatment	✓	✓	
Chew health literacy measure (one item)	✓	✓	
Patient demographics (email address, health insurance status, age, race, gender, and spoken language)	✓	✓	

Throughout the pre- and active implementation phases, eligible patients at each site will be invited by clinic staff to take a survey on a tablet computer following their clinical encounter (see Additional file 2 to view the patient survey). Clinic staff may provide the patient with the tablet computer or refer them to a kiosk located in the clinic that will contain the tablet. At the start of the survey, patients will be given the opportunity to view the study information and provide consent to participate in the study. The survey will collect the following patient-reported outcomes, in addition to the patient’s email address which will be used to send patients a WebLink to the follow-up survey 3 months after their first survey is completed. The follow-up survey can be completed on a personal computer or mobile device. We anticipate that approximately 30% of eligible patients will complete the post-encounter survey. The following is a list of patient-reported outcomes that we will be assessing:

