#### Data analysis

Patient-level data will be clustered by site and clinician. Patients will be assigned to a single phase based on the date of their first encounter with a clinician at the site during the project period. Instances in which a patient has a repeated visit in the pre- and active implementation periods will be recorded to enable sensitivity analyses accounting for repeated observations.

Regression analyses will compare quantitative outcome measures (including survey scores and Option Grid use) between the pre- and active implementation phases while adjusting for patient and clinician characteristics. The extent to which clinicians involve patients in decision-making for each recorded encounter will be assessed by analyzing the Observer OPTION-5 and Option Grid fidelity checklist data from each phase of the study. We will conduct a framework analysis, guided by NPT, of the clinician interview transcripts to determine the barriers and facilitators of Option Grid implementation. Completion of the NoMAD Normalization Process Theory survey, based on interviews with site stakeholders, will enable us to make across-site assessments of implementation sustainability.

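### As described, the primary-outcome numerator counts tools dispensed, with no stated link to the list of eligible patients that forms the denominator

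*Protocol article*

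**What the plan says.** Protocol article, Primary outcome measure. On the denominator: "Eligible patients will be identified in advance by the project team at each site through their outpatient scheduling systems". On the paper numerator, pads lie in all consultation rooms. When a clinician tears off a sheet, "a numbered stub will remain where they will write their name and indicate if they are an attending clinician or a resident". The research assistant reads the stubs weekly and records them as the number of patients who received the tool. For sites with EHR access, the text after Fig. 3 adds: "we will derive weblog data from EBSCO Health including the date and time the tool was generated". These data feed into the primary outcome.

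Delivery routes. Three formats exist (text, picture, online), and each site chooses which to use (section on initiation). Table 1, under Networks and communication, adds: "Where possible, the eligible patients will be sent an Option Grid in advance of their appointment". Elsewhere Table 1 names the online tool as one that can be sent ahead of or after visits.

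Use of the outcome. Table 2 lists it as a percentage of eligible patients. Power calculation gives Option Grid use as an example of a binary dependent variable, with 2600 patients and a margin of 0.048. Data analysis plans regression of outcomes that include Option Grid use, comparing the pre- and active implementation phases "while adjusting for patient and clinician characteristics". It also assigns each patient to one phase by the date of the first encounter.

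**The concern.** A percentage of eligible patients needs a numerator drawn from the same people as its denominator. A patient-adjusted model of a binary outcome needs a yes or no for each identified patient. The stated procedure yields neither. It yields a count of torn sheets and generated pages, set against a list compiled separately.

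The count can be too high. A sheet given to an ineligible patient, two formats for one patient, paper plus online for one patient, and a sheet at a repeat visit can each be entered as a patient. It can also be too low. Paper sent ahead without a completed stub, and online use at a site without EHR access, may leave no trace in either record.

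What is at stake is the primary outcome itself. Sites choose their own formats and differ in EHR access, so the error need not be the same across sites, and comparing sites is central to an implementation study. A link that was never recorded cannot be restored at the analysis stage.

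**Working it through.** **Step 1. The plan's own margin.** Inputs from Power calculation: 2600 patients, baseline proportion 0.5, margin 0.048, 80%. An equal split of 1300 per phase is assumed, from the two 6-month phases.

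- SE = sqrt(0.25/1300 + 0.25/1300) = 0.0196.
- (1.645 + 0.842) × 0.0196 = 0.0488, close to the stated 0.048. This uses a one-sided 5% multiplier.
- The two-sided multiplier gives (1.96 + 0.842) × 0.0196 = 0.0549.

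The point here does not depend on which multiplier was meant. The figure 0.048 serves only as the plan's own yardstick of precision.

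**Step 2. What each planned use needs, against what is recorded.**

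- Percentage of eligible patients (Table 2): needs a numerator inside the eligible list. Recorded: stub number, clinician name and grade, and generation date and time. No match to the list is described.
- Binary use per patient (Power calculation): needs a value, including a no, for every listed patient. A pile of stubs gives a total and does not show which patients received nothing.
- Adjustment for patient characteristics (Data analysis): needs the patient behind each stub. Stubs can be grouped by clinician and week, but not by patient.
- Phase by first encounter (Data analysis): a patient first seen in the pre-implementation phase who returns in the active phase belongs to the earlier phase, yet her sheet is counted in the later one. Unlinked stubs cannot apply the rule.

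**Step 3. Size of the error under assumed rates.** Let N be the eligible patients, R the true share who receive the tool, m the share of recipients not captured, and d the share of counted tools that do not go to a distinct eligible patient. The count C satisfies C(1 − d) = R·N·(1 − m), so

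observed share = C/N = R(1 − m)/(1 − d).

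The documents give no values for R, m or d; those below are assumptions. At R = 0.5:

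- d = 10%, m = 0: 0.5/0.9 = 0.556, error +0.056.
- d = 20%, m = 0: 0.5/0.8 = 0.625, error +0.125.
- d = 0, m = 10%: 0.5 × 0.9 = 0.450, error −0.050.
- d = m: the errors cancel.

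Rates that give an error equal to 0.048, from d = 1 − R/(R + 0.048) with m = 0, or m = 0.048/R with d = 0:

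- R = 0.3: d = 13.8% or m = 16%.
- R = 0.5: d = 8.8% or m = 9.6%.
- R = 0.7: d = 6.4% or m = 6.9%.

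Two sites, both with 50% true reach, one with d = 10% only and the other with m = 10% only, would report 55.6% and 45.0%. That is an apparent gap of 10.6 points where there is none.

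**Step 4. If patient-level use came only from the survey.** The article expects about 30% of eligible patients to complete it. 0.30 × 2600 = 780, or 390 per phase. SE = sqrt(2 × 0.25/390) = 0.0358, and (1.645 + 0.842) × 0.0358 = 0.089, against 0.0488 in Step 1.

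**The case against.** The strongest reply is that a journal article condenses the full protocol, and matching rules may sit there. The Fig. 3 mockup is not visible, and the weblog fields are introduced as an open list, so a patient field cannot be ruled out. The same research assistant logs numerator and denominator each week and could match them informally. This stands as a limit on certainty. It does not remove the point, because the article states what the clinician writes on the stub and that stubs are recorded as patients. As written, that procedure does not give what Table 2, Power calculation and Data analysis need.

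A reader might infer that all tools sent ahead are missed. The documents do not support that. Table 1 names the online tool for advance sending, and generations at sites with EHR access are logged. Only paper without a completed stub, and online use at sites without EHR access, may be lost. A logged generation does not, however, show receipt.

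A reader might also infer that the patient-adjusted analysis is impossible. That goes too far. Patient-reported use (Table 1), the standard EHR phrase (Intervention) and the fidelity checklist on recorded visits could give partial patient-level data. None is assigned to the primary numerator, survey completion is expected at about 30%, and recordings are a sample.

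Two further readings fail. Calling the outcome a number in the text and a percentage in Table 2 is not a real conflict, because the text itself defines a numerator and a denominator. Whether the criterion "have the ability to complete short surveys online independent of assistance" should restrict the denominator is a separate design preference.

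Finally, the miscount rates are assumed, nothing in the article suggests that double issue is routine, and over- and under-counts can offset. That is correct, and it is why no size is claimed as fact.

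**Conclusion.** The point holds in this form: followed as written, the procedure counts tools dispensed, not distinct eligible patients. The numerator is not guaranteed to be a subset of the denominator, and the stub and weblog records alone cannot supply the per-patient outcome or the patient-adjusted, first-encounter analysis. The direction and size of the error are unknown. At 50% true reach, a miscount of about 9 to 10% in one direction is enough to match the stated 0.048 margin. This rests on the assumed rates shown, on no offsetting error, and on the records holding no patient field beyond those described. The illustration does not show that reach will be wrong by any given amount; it shows that the recorded data could not reveal such an error. It deserves correction before data collection because the link cannot be recovered afterwards.

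**What to change.** Let the existing weekly log hold one row per patient on the eligible list, with appointment date, clinician, a yes/no receipt flag and the format. Put a coded eligible-list or appointment number, with no direct identifier, on each stub and on the record of each online or advance-sent tool. Count each eligible patient once, and report the primary outcome as that proportion.

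Consent is taken at the start of the tablet survey, which about 70% of eligible patients are not expected to complete. If linkage is not permitted for patients who have not consented, name the outcome tools dispensed per eligible patient. Analyse it as clinician-week or site-week counts against the eligible number, without patient covariates, and state that it can include repeat or ineligible recipients.

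Cost: a changed stub and log template, one code per sheet, some incomplete stubs (report how many), and a check that the ethics approval covers the coded link. The same research assistant and weekly reporting can be kept.

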**Fig. 3 Fig3:**

Paper-pad mockup to identify the number of eligible patients receiving the uterine fibroid Option Grid in the clinic

For sites with EHR access to the online uterine fibroid Option Grid, we will derive weblog data from EBSCO Health including the date and time the tool was generated; this data will be incorporated into measurement of the primary outcome.

#### Secondary outcome measures

In addition to recording each site’s chosen implementation strategy and if/how it changes during the implementation and sustainability phases, we will collect the following secondary outcome measures (as outlined in Table 2):
*Measuring Organizational Readiness for patient Engagement (MORE)***.** MORE is designed to measure a healthcare organization’s willingness and ability to effectively implement patient engagement in healthcare [29]. The measure contains 25 items that are each scored on a four-point Likert-type scale (1 = avoid/not important; 4 = definitely involve/very important) [29]. Data from the measure will be analyzed to identify barriers and facilitators to implementation at each site and tailor the implementation strategy accordingly.Each site PI will be asked to nominate 20–30 MORE recipients within their department. Dartmouth study staff will then email the online survey link to nominees in the 2 months preceding the pre-implementation phase at each site.*Attitudes toward Decision Aids fOr PatienTs (ADOPT).* ADOPT is a measure of patient attitudes and perceptions toward PDAs. Clinicians are asked to select one or more words that best describe(s) their attitudes to the potential use of PDAs from a pool of 10 words. It can be completed by clinicians who have, or have not, used PDAs.ADOPT will be administered to all participating clinicians at three time points: (i) the start of the pre-implementation phase, (ii) the end of the active implementation phase, and (iii) the end of the sustainability phase. The surveys will be distributed via email to participating clinicians using a secure web link.*Extent of shared decision making.* Observer OPTION-5 is a validated, observational measure. It is a five-item scale, with each item rated from “0” to “4” where “0” represents the absence of a shared decision-making specific competency and “4” represents optimal performance [30].A research assistant employed at each site will audio-record five clinical encounters in both the pre- and active implementation phases for each participating clinician that consents to audio-recording. In each phase, we will establish a recruitment day(s) each week where a research assistant will approach as many eligible patients as possible to seek consent to audio-record their visit. This will be repeated each week until five encounter recordings per clinician per phase are obtained (10 per clinician in total). In the active implementation phase, we will begin the audio-recording recruitment process described above 2 months into the phase to allow clinicians time to get comfortable and confident with the intervention prior to recording. We will consult with sites to determine if we will audio-record encounters that take place between residents and patients. We anticipate a patient consent rate of 50 to 60% [31].*Fidelity of intervention use*. The fidelity assessment checklist enables us to determine if an Option Grid was used, how and when it was delivered to the patient, whether or not the clinician made a treatment recommendation or elicited patient preference, and the identification of the final treatment decision [32]. The checklist will help us understand if clinicians are using the tools as intended following initiation.The checklist will be completed independently by two Dartmouth-based project staff while listening to the audio-recorded clinic visits.*NoMAD Normalization Process Theory (NPT) survey.* A 23-item instrument used for capturing the perspective of professionals who will be involved in implementing and using Option Grid in practice [33]. The instrument contains four sections that ask questions on the various facets of implementing and using the intervention such as the effect that it has on workflow, the work and resources needed to drive implementation, and critical appraisal of the Option Grid.A convenience sample of 10 stakeholders at various levels of the service delivery team (i.e., clinicians, medical assistants, nurses, coordinators, managerial and reception staff) from each site will have the opportunity to complete the NoMAD survey at two time points: (i) at the end of the pre-implementation phase and (ii) at the end of the sustainability phase. Participants will be asked to provide their name each time they complete the survey. Stakeholders can complete the survey during a site visit, or they will have the opportunity to complete it online after the project team at Dartmouth sends a secure WebLink via email.*Utility of Option Grid PDAs and clinician approach to implementation*. Semi-structured interviews, guided by NPT, will be conducted with clinicians to assess the utility of the Option Grid tools and how they implemented the intervention in practice.A member of the project team at Dartmouth will conduct semi-structured interviews in-person or via phone with a convenience sample of clinicians at each of the five clinical sites to determine the utility of the uterine fibroid Option Grid PDA and the barriers and facilitators to its integration in the clinic workflow at two time points: (i) at the end of the active implementation phase and (ii) at the end of the sustainability phase.

**Table 2 Tab2:** Implementation sustainability outcome measures for patient outcomes

	Implementation phases		
	Pre	Active	Sustainability
Organizational readiness (Measuring Organizational Readiness for patient Engagement survey)	✓		
Clinician attitudes to PDAs (ADOPT: Attitudes toward Decision Aids fOr PatienTs survey)	✓	✓	✓
Percentage of eligible patients receiving intervention (primary outcome measure)	✓	✓	✓
Quality of shared decision-making process using Observer OPTION-5	✓	✓	
Utility of tools and approach (clinician interviews)		✓	✓
Normalization Process Theory: NOMAD Toolkit (interviews)	✓		✓
Intervention fidelity assessment using observer checklist		✓	
Patient outcomes			
Uterine Fibroid Symptom and Health-Related Quality of Life Questionnaire (UFS-QOL) symptom severity subscale (8-items)	✓	✓	
**collabo**RATE (three items)	✓	✓	
The Comprehensive Score for financial Toxicity (COST)—one selected item	✓	✓	
Resource utilization (ambulatory and hospital visits)	✓	✓	
Intended and received treatment	✓	✓	
Chew health literacy measure (one item)	✓	✓	
Patient demographics (email address, health insurance status, age, race, gender, and spoken language)	✓	✓	

Throughout the pre- and active implementation phases, eligible patients at each site will be invited by clinic staff to take a survey on a tablet computer following their clinical encounter (see Additional file 2 to view the patient survey). Clinic staff may provide the patient with the tablet computer or refer them to a kiosk located in the clinic that will contain the tablet. At the start of the survey, patients will be given the opportunity to view the study information and provide consent to participate in the study. The survey will collect the following patient-reported outcomes, in addition to the patient’s email address which will be used to send patients a WebLink to the follow-up survey 3 months after their first survey is completed. The follow-up survey can be completed on a personal computer or mobile device. We anticipate that approximately 30% of eligible patients will complete the post-encounter survey. The following is a list of patient-reported outcomes that we will be assessing:

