### Statistical analysis

#### Power calculation

The primary analysis has an expected sample size of 2600 patients across 30 to 40 clinicians (an estimated 87 patients per clinician [*n* = 30]) at each of the five sites. Because the intervention varies within clinician and our statistical models include clinician random and site-fixed effects, the relevant clustering variable is clinician-project week. With 40 project weeks and at least 30 clinicians, clustering is likely to have minimal impact on the results. Therefore, for a binary dependent variable (e.g., whether the uterine fibroid Option Grid is used or whether the patient gives a top **collabo**RATE score) with a baseline proportion of 0.5, a symmetric two-sided 95% confidence interval of width of at least 0.048 will have an 80% coverage probability of containing the true effect of the intervention, i.e., attaining a confidence margin of 0.048. In the context of shared decision making, such a margin is small and below typical levels of precision obtained from randomized studies.

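### One precision figure (0.048 at n = 2600) is given for both Option Grid use and top collaboRATE score, although only about 30% of eligible patients are expected to supply a collaboRATE score

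*Protocol article*

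**What the plan says.** All places are in the protocol article.

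- **Power calculation.** The sample is tied to the primary analysis: "The primary analysis has an expected sample size of 2600 patients across 30 to 40 clinicians". The precision statement then covers a binary variable and names two examples: "whether the uterine fibroid Option Grid is used or whether the patient gives a top" collaboRATE score. Its inputs are stated as "with a baseline proportion of 0.5" and "a symmetric two-sided 95% confidence interval of width of at least 0.048", with an 80% probability attached. Clustering is taken to have little effect. The section calls the resulting margin small by the standards of shared decision-making research.
- **Primary outcome measure.** Eligible patients are found in advance from scheduling systems, and these form the denominator: "This process will enable us to determine the total number of patients who are eligible to participate in the study (the denominator"). Receipt of the Option Grid is counted from pad stubs and weblogs. No patient survey is needed.
- **Secondary outcome measures.** collaboRATE is one of the patient-reported outcomes in the tablet survey offered after the encounter in the pre- and active implementation phases. On response, the article says: "We anticipate that approximately 30% of eligible patients will complete the post-encounter survey".

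**The concern.** The two named outcomes do not share a sample. Option Grid receipt is observed for every eligible patient, whereas a collaboRATE score exists only for those who complete the survey. A single n and a single margin cannot describe both unless completion is close to complete, and the article itself expects about 30%.

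At stake is how precisely the pre-versus-active change in collaboRATE can be estimated. A reader who takes 0.048 at face value expects a confidence margin of about 5 percentage points for that outcome. On the article's own completion rate it would be nearer 9. The remark that the margin is small is carried over to an outcome for which it was not worked out.

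**Working it through.** **Inputs**

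- n = 2600, baseline proportion 0.5, two-sided 95%, 80% probability, margin 0.048, negligible clustering: Power calculation.
- Completion 0.30: Secondary outcome measures.
- Equal phase sizes: my assumption. The Abstract gives 6 months to each of the two phases but no numbers of patients.

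**Step 1. The article's own figure.** For a difference of two proportions with 1300 patients per phase:

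SE = sqrt(0.25 × 2/1300) = 0.0196

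| Formula at n = 2600 | Result |
|---|---|
| Two-sided 95% half-width, 1.96 × SE | 0.038 |
| Full width of that interval | 0.077 |
| Two-sided 5%, 80% power, (1.96 + 0.842) × SE | 0.055 |
| One-sided 5%, 80% power, 2.486 × SE | 0.049 |

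The stated two-sided inputs do not give 0.048. The one-sided version comes close but contradicts the two-sided interval in the text. A 95% half-width with an 80:20 phase split also gives 0.048, but no such split is stated. So 0.048 is not reproduced, and the next steps do not depend on knowing its source.

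**Step 2. Expected collaboRATE responses.** If 2600 counts eligible patients:

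0.30 × 2600 = 780, or 390 per phase

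**Step 3. Effect on the stated margin.** At a fixed phase split and design effect, every formula above is proportional to 1/sqrt(n). The ratio is therefore

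sqrt(2600/780) = sqrt(1/0.30) = 1.83

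and 0.048 × 1.83 = 0.088.

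**Step 4. The same change under the standard formulas.** At n = 780, SE = sqrt(0.25 × 2/390) = 0.0358.

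| Formula | n = 2600 | n = 780 |
|---|---|---|
| Two-sided 95% half-width | 0.038 | 0.070 |
| Two-sided 5%, 80% power | 0.055 | 0.100 |
| One-sided 5%, 80% power | 0.049 | 0.089 |

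**Step 5. Sensitivity to the completion rate.** For an assumed range of 25% to 40%, n runs from 650 to 1040, and the rescaled margin from 0.048/sqrt(0.25) = 0.096 to 0.048/sqrt(0.40) = 0.076.

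**Step 6. The reverse reading.** If 2600 counts survey completers, the eligible number implied is 2600/0.30 = 8,667. The article gives no such number.

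**The case against.** **2600 may already be survey completers.** The Power calculation says patients, not eligible patients. Patients consent at the start of the survey, and demographics are collected there. The Data analysis section adjusts for patient characteristics, and the pad stub is described as carrying a number and clinician details only. An adjusted patient-level model might therefore rest on respondents. On that reading 0.048 is not understated for collaboRATE and is conservative for receipt among all eligible patients. This stands as a possibility, so 780 is conditional. It sits badly, though, with the label of primary analysis and the eligible-patient denominator. It also leaves 2600 as the wrong n for the other named outcome.

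**2600 may be per site.** The sentence ends by referring to each of the five sites. Five times 2600 is 13,000 eligible patients and 3,900 completers, which is more than 2600. The 87 patients per clinician does not settle this by itself, since 2600/30 = 87 whether both figures are totals or both are per site. But the next lines speak of at least 30 clinicians when describing the study's clustering. At 13,000 the two-sided formulas give 0.017 to 0.025, far from 0.048. A total of 2600 is the better reading, and on either reading the two outcomes differ in n by the same factor.

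**collaboRATE is only an example, and a secondary outcome.** Correct. A reader might infer that the study's main effect is imprecise, or that a null collaboRATE result would be misread. The article does not call collaboRATE the main effect and attaches no decision rule to 0.048, and a result would be judged by its observed interval. A power figure for a true difference of 0.048 would likewise go beyond the text, which presents 0.048 as a margin and not as a target effect.

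**This could be left to an analysis plan.** Not here: the article states a precision for collaboRATE and, in another section, a completion rate that does not fit it.

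**Conclusion.** The point holds in a limited form. The margin of 0.048 at n = 2600 cannot serve both Option Grid use and top collaboRATE score. Reading 2600 as eligible patients, as the text indicates, about 780 collaboRATE responses are expected and the margin is 1.83 times as large, about 0.088 on the article's scale.

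This rests on the 30% completion rate and on the same phase split and negligible clustering at both sample sizes. The 0.070 and 0.100 figures also assume equal phases and p = 0.5, and they come from formulas that do not return 0.048.

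Two stronger inferences are not supported:

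- **That 0.07 or 0.10 applies to every survey outcome.** These are differences in proportions. The symptom severity subscale, the financial worry item and the visit counts are not binary, so only the reduced n carries over to them.
- **That the primary outcome is affected.** On the reading adopted here, receipt of the Option Grid keeps n = 2600, and this point does not touch the design or recruitment.

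Nor do the documents give a benchmark showing that 0.09 is not small. What can be said is that the remark was not made about that figure.

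**What to change.** In the Power calculation:

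1. Say whether 2600 counts eligible patients or survey completers, and whether it is a total over the five sites.
2. If it counts eligible patients, state precision separately: n = 2600 for Option Grid receipt, and about 780 for top collaboRATE score, with a margin of about 0.09 on the article's scale before clustering. Give the formula and phase split used. If 0.048 is itself recalculated, multiply the new value by 1.83 for collaboRATE.
3. Confine the remark that the margin is small to the outcome for which it was computed.
4. For the other post-encounter survey outcomes, state only that about 780 responses are expected, and no more than that at the 3-month follow-up. Do not attach the binary margins to non-binary scales.
5. If 2600 counts survey completers, say so and give the eligible number implied, about 8,670, as the sample for the primary outcome.

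The cost is restated figures and a few sentences. No patients, visits or data collection are added.
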